### Study population and sample procedures

We will select an age-stratified random sample of participants aged ≥30 years from the population registers of the Kiang West Health and Demographic Surveillance System (KWHDSS, the Gambia) and Kilifi Health and Demographic Surveillance System (KHDSS, Kenya)
^
43,
44
^. Half of the study population will be selected from The Gambia and half from Kenya. The following age strata will be used: ≥30 to <40, ≥40 to <50, ≥50 - <60, ≥60 - <70 and ≥70y.

Pregnant women will be excluded due to technical difficulties in conducting some of the study measurements such as the echocardiogram and while gestational hypertension remains important it is beyond the scope of our aims and objectives. The participant recruitment approach is shown in
Figure 2.

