### Study aim and objectives

We aim to improve the evidence base for diagnosis and risk estimation for a CHW-led community-centred hypertension programme in two rural communities in SSA.

We have the following specific objectives:

1. To determine the accuracy of three alternative blood pressure measurement methods relative to the reference standard and establish the prevalence of hypertension2. To determine the relationship between systolic blood pressure and potential risk factors3. To determine the prevalence of HMOD4. To determine the accuracy of innovative POC technologies to identify patients with HMOD5. To estimate the likely cost-effectiveness of different combinations of blood pressure and HMOD measurements to initiate pharmacological treatment in people with hypertension

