### Sample size

The overall sample size for the study is based on the assessment of hypertension prevalence. Assuming a prevalence of hypertension of 25–35%, as detected by the reference standard method (24-hr-ABPM), we will require 832–1003 participants to generate validity parameters for hypertension prevalence with a precision of ±3% overall and ±5% at each of the two sites
^
24,
41
^. We have made a provision for loss of data in 25% of participants due to poor data quality, taking the total number of participants required to 1250, equally divided between Kilifi (N=625) and Kiang West (N=625). This overall sample size will provide sufficient statistical power to address the other aims stated above.

In our assessment of BP and risk factors, and assuming for illustrative purposes that 10% of individuals will have any of the putative factors and that the standard deviation of systolic blood pressure will be 15 mmHg, then 1,003 participants will provide at least 80% statistical power for an alpha of 0.05 to detect a 4mm Hg difference in systolic BP in those with and without the exposure of interest.

Assuming a prevalence of hypertension detected by the reference standard method (24-hr-ABPM) of 30%, we estimate that approximately 300 participants from those recruited in Objective 1 will be classified as hypertensive. With 300 hypertensive patients, we would be able to estimate the confidence interval for a conservative HMOD prevalence of 35% with lower and upper intervals of 29.7% and 40.4% respectively, and that we will have over 95% power for an alpha of 0·05 to test the null hypothesis that the prevalence of HMOD is below 25%. To further explore the difference in the prevalence of HMOD in the hypertensive and general population, we intend to assess all participants recruited into the study for HMOD.

When measured with the reference standard techniques, we expect a 35% prevalence of HMOD among the 300 estimated hypertensive participants and approximately 5% prevalence in the remaining non-hypertensive participants. This will provide us with a total available sample of 153 participants with HMOD. Assuming at least 85% sensitivity of detection of HMOD by the POC strategies we will have at least 80% power for an alpha of 0.05 to test the null hypothesis that the sensitivity is below 75%. As above, we will conduct POC HMOD assessments on all participants.

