### Statistical analysis plans

A detailed statistical analysis plan will be produced before data collection is completed and uploaded to a public repository. A summary of statistical analysis approaches that will be taken for this study is outlined here.

**
*Hypertension prevalence*.** We will estimate sensitivity; specificity; positive and negative predictive values; and the positive and negative likelihood ratios of each BP measurement approach compared to the reference standard 24-hour BP measurement method.

**
*Identifying hypertension risk factors*.** The primary outcome will be hypertension, defined as a BP of >140/90mmHG using 24-hour BP measurement, or ongoing therapy with anti-hypertensives. We will determine the relationship between the candidate risk factors and blood pressure and hypertension using multivariate linear and logistic regression methods as appropriate. We will include confounders in the regression models based on results of univariate models and existing literature on the subject.

**
*Prevalence of organ damage*.** We will analyse the overall prevalence of HMOD and report age- and sex-standardised and stratified prevalence rates. We will also analyse prevalence rates stratified by type of HMOD (left ventricular hypertrophy, impaired left ventricular systolic function, renal dysfunction, hypertensive retinopathy, or arterial stiffness). Finally, we will construct logistic regression models to identify the participant parameters associated with presence of HMOD.

**
*Accuracy of POC diagnostic tools*.** The diagnostic accuracy of the POC assessments will be estimated using sensitivity; specificity; positive and negative predictive values; and positive and negative likelihood ratios of each POC parameter compared to the conventional measurement. These comparisons will be:

1) Left ventricular systolic function: Smartphone-based ECG (analysed with Mayo Clinic trained AI algorithms) compared to transthoracic echocardiogram (reference standard).2) Left ventricular hypertrophy: Smartphone-based ECG (analysed with validated and trained AI algorithms) compared to 12-lead ECG and transthoracic echocardiogram (reference standard).3) Hypertensive retinopathy: Smartphone-based retinal imaging compared to clinical grade retinal camera (reference standard) in detecting HMOD.4) Renal dysfunction: POC clinical chemistry and urinalysis dipstick compared to conventional clinical laboratory assessment of blood and urine markers for renal function

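### Confounders for the Objective 2 risk-factor models are chosen partly from univariate results, which can drop a masked confounder or add a mediator; the likely bias is small to moderate and the fix is one sentence

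*Protocol article*

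**What the plan says.** Objective 2 is stated as "To determine the relationship between systolic blood pressure and potential risk factors" (Study aim and objectives). The paragraph on identifying hypertension risk factors, under Statistical analysis plans, relates the candidate factors to blood pressure and hypertension "using multivariate linear and logistic regression methods as appropriate". It then gives the covariate rule: "We will include confounders in the regression models based on results of univariate models and existing literature on the subject".

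The rule names two sources. It gives no significance threshold, does not say how the sources combine, and lists no variable that is adjusted for regardless. No other section limits it.

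Two further points of context:

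- Sampling is stratified by age ("The following age strata will be used", followed by five bands from 30 years upwards) and split equally between the two countries (Study population and sample procedures).
- The analysis section is a summary: "A detailed statistical analysis plan will be produced before data collection is completed".

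**The concern.** In Objective 2 the adjusted association is itself the result, so the choice of adjustment variables decides what is estimated. A confounder is defined by its relation to both exposure and outcome. Its crude association with the outcome alone does not reveal this, for two reasons:

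- **Masking.** If a confounder lowers blood pressure but is commoner among people with an exposure that raises it, the two effects partly cancel in the univariate model. The confounder looks null and may be left out, and the exposure effect is then underestimated.
- **Mediation.** A variable on the path from exposure to blood pressure can look strong in a univariate model and be added. That removes part of the effect under study.

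Age stratum and site are also features of the design, so their place in the models should not depend on a test. What is at stake is the size of individual risk-factor estimates and, in some configurations, the coverage of their confidence intervals.

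**Working it through.** **The plan's own figure.** The only number attached to Objective 2 is its power statement: "1,003 participants will provide at least 80% statistical power for an alpha of 0.05" for a 4 mmHg difference, assuming "10% of individuals will have any of the putative factors" and "the standard deviation of systolic blood pressure will be 15 mmHg". With 902.7 unexposed and 100.3 exposed, the normal approximation gives 81.3% for a one-sided alpha of 0.05 and 71.7% for a two-sided one. The stated figure is therefore reproduced one-sided only, and the article does not state sidedness. That is a separate matter; the present point does not rest on it.

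**Inputs for the check.** From the Sample size section: effect 4 mmHg, SD 15 mmHg, 10% exposed, and 1,250 recruited with 25% data loss, so 0.75 × 1,250 ≈ 937 evaluable. Assumed, because the article gives no such values: one binary confounder C present in half the sample, its effect on systolic pressure, its link to exposure, and a screen that keeps C only if its univariate p-value is below a threshold. Literature plays no part in this screen.

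**How often the screen drops C (p<0.05).** The expected crude difference by C is: effect of C + 4 × (exposure prevalence at C=1 − exposure prevalence at C=0). Its standard error is about 15 × √(4/937) = 0.98. The chance of dropping C is Φ(1.96 − |z|) − Φ(−1.96 − |z|).

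- Exposure 10% v 40%, C = −2: −2 + 4 × 0.30 = −0.8, z = −0.82, dropped in about 87%.
- Exposure 5% v 15%, C = −2: −2 + 4 × 0.10 = −1.6, z = −1.63, dropped in about 63%.
- Exposure 5% v 15%, C = −5: −5 + 0.4 = −4.6, z = −4.69, dropped in about 0.3%.

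**Bias if C is always left out.** This is the effect of C × [P(C=1 | exposed) − P(C=1 | unexposed)].

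- 10% v 40%: −2 × (0.40/0.50 − 0.60/1.50) = −2 × 0.40 = −0.80 mmHg.
- 5% v 15%: −2 × (0.15/0.20 − 0.85/1.80) = −2 × 0.278 = −0.56 mmHg.

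Under screening the average bias is smaller than this, because C is kept in some samples and is dropped mainly where its estimated effect happens to be weak. Simulation (4,000 datasets per scenario, N = 937, true effect 4) gives:

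| Exposure at C=0 v C=1 (overall) | Effect of C | Screen | C dropped | Mean estimate | 95% CI coverage |
|---|---|---|---|---|---|
| 10% v 40% (25%) | −2 | p<0.05 | 88% | 3.39 | 92% |
| 10% v 40% (25%) | −2 | p<0.20 | 67% | 3.59 | – |
| 5% v 15% (10%) | −2 | p<0.05 | 62% | 3.76 | 95.0% |
| 5% v 15% (10%) | −2 | p<0.20 | – | 3.86 | 95.5% |
| 5% v 15% (10%) | +2 | p<0.05 | – | 4.09 | 95.0% |
| 5% v 15% (10%) | −5 | p<0.05 | 0.4% | 3.99 | 95.3% |

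A dash marks a value that is not reported here. With C always included, the 10% v 40% case gives a mean of 4.02 and 95% coverage. Repeat runs of the third row gave 3.75 to 3.77, and of the fourth up to 3.91.

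**A different confounder.** With N = 1,003, 10% exposed, a continuous confounder and p<0.05:

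- 1 SD higher in the exposed, −1 mmHg per SD: dropped in 68%, mean 3.43, coverage 93.7%.
- 1.5 SD higher, −1 mmHg per SD: dropped in 76%, mean 3.05, coverage 89.9%.
- 1 SD higher, +1 mmHg per SD: dropped in 16%, mean 4.04.

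The strength of the link between confounder and exposure, together with opposite sign and a weak effect, drives the bias. Exposure prevalence alone does not. Adding a mediator was not simulated.

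**The case against.** The strongest reply is that the calculation tests a rule the article does not state. The article names literature as well as univariate results, sets no threshold, and does not say that a null result excludes a variable. If every literature-supported confounder stays in, only confounders that the literature does not name can be lost. This stands as a limit on size. It does not remove the point: the text does not say so, and univariate results would still be a route for adding mediators.

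A second reply is that this is a summary and the named adjustment set belongs in the later analysis plan. That is right about the list of covariates, and its absence is not criticised here. But using univariate results is a method that the article states, and an analysis plan that followed it would carry it forward.

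Third, material bias needs a particular configuration. At 5% v 15% the shift of about 0.25 mmHg is small against a standard error near 1.65 mmHg, and root mean squared error is 1.66 with screening v 1.65 with C always included. This also stands.

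Three stronger readings are tempting but unsupported:

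- *Age or site will be dropped.* Nothing says so, and a confounder with a large effect on blood pressure almost always passes a screen.
- *The estimates will be about 15% too low with intervals too narrow throughout.* That figure (0.61/4) belongs to the 10% v 40% case, which implies 25% exposure overall rather than the planned 10%. Coverage is nominal in the 5% v 15% case.
- *Masking is known to affect genotypes, diet or household assets.* The article reports no association of these with site or age, and names no mediator.

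**Conclusion.** The point holds as a weakness in a stated method. Univariate results are a poor basis for choosing confounders, and the article does not protect literature-supported confounders from a null univariate result.

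Under a pure p<0.05 screen and a confounder of −2 mmHg, the bias is about 0.25 mmHg of 4 with nominal coverage at 10% exposure (5% v 15%), and about 0.6 mmHg with 92% coverage at 10% v 40%. An extreme link (1.5 SD, −1 mmHg per SD) takes it to about 0.95 mmHg with 90% coverage. A looser screen reduces the bias. It is near zero for strong confounders or those acting in the same direction as a real effect. All of these sizes rest on assumed confounder values and on giving literature no role, so they illustrate what can happen and do not forecast this study's results.

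Only the Objective 2 risk-factor models are shown to be affected. The prevalence and diagnostic-accuracy estimates involve no confounder selection, and the article does not feed Objective 2 estimates into the cost-effectiveness model. The sentence should be changed, but it does not threaten the study.

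**What to change.** Replace the covariate sentence, in the protocol and in the statistical analysis plan, with:

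> Adjustment sets will be fixed in advance for each candidate risk factor from existing literature and a causal diagram, and will always include age, sex and site; univariate results will be reported descriptively and will not be used to select or exclude covariates.

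The causal diagram also settles, exposure by exposure, which variables are mediators and should stay out of the total-effect model.

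The cost is a few degrees of freedom: with five age bands, sex and two sites, 4 + 1 + 1 = 6 out of about 937 evaluable participants, plus the variables chosen for each exposure. No new data are needed beyond what the diagram calls for among variables already collected. The analysis plan is due before data collection ends, so the change can be made there. If that plan already exists, check that it does not repeat the univariate rule.

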### Ethical considerations

**
*Approval for research involving humans*.** Ethical approval for this research has been given by the KEMRI Scientific & Ethics Review Unit (SERU4620; 6 February 2023), the MRCG Ethics Committee and the LSHTM Ethics Committee (28276; 6 March 2023).

**
*Consent*.** We will obtain written informed consent from all the study participants. CHWs will be trained in the consenting procedures and will be responsible for obtaining consent. We will put in place all the necessary measures to remove potential barriers for informed consent, including language, literacy, and pressure to participate to access care.

All study participants will be provided with comprehensive information about the study in the language they are most comfortable with. This information will explain the study's aims, their specific role in it, and how data being collected will be used. Where a participant is illiterate an independent witness will be present to ensure the correct study information is presented to the participant. This witness will sign the consent form as well.

It will be made clear that participation in any part of the research will be entirely voluntary, will not influence future care and that participants will be free to withdraw at any stage, without giving a reason.

**
*Withdrawals*.** Participants may withdraw from the study at any time, for any reason. The study team may withdraw participants if they are no longer contactable or if they develop conditions that would exclude them from the study, including a lack of capacity to consent.

**
*Compensation*.** Participants will not be compensated for home blood pressure measurement visits as they will not disrupt daily activities and will take less than 15 minutes. Participants will be compensated for their time and expenses to attend hospital visits. For each visit, participants will be reimbursed 500 Kenyan shillings or 250 Gambian dalasi plus any travel expenses incurred traveling to and from the research visit.

**
*Urgent care referral*.** During this research, it is possible that severe medical conditions could be identified. In such cases we will arrange for urgent care and further treatment will follow the locally available standard of care.

## Discussion and expected value of results

This study is part of the wider IHCoR-Africa research group. The outcomes of this specific study will deliver the strongest evidence to date about different diagnostic approaches for hypertension in rural SSA, a unique understanding of the prevalence and characteristics of HMOD in this population, and a robust assessment of the role of innovative, low-cost, POC devices to manage hypertension in rural SSA. In addition, it will provide novel evidence of hypertension phenotypes in rural SSA. The impact of this study (together with other activities of IHCoR-Africa) will improve the long-term health outcomes of people living with hypertension in SSA.

One of the main strengths of IHCoR-Africa is the strong engagement with the community and key stakeholders. The research team has secured support from governmental organizations, civil society, scientific societies, health care providers, and patient groups. Their active engagement in IHCoR-Africa activities before and during the study will be our first step to ensuring early engagement and targeted dissemination of the results. We will present study outputs in scientific meetings of our partners including PASCAR, KCS and AESA and seminars run by the partner institutions. The
IHCoR-Africa website, provides up-to-date information on the progress of the study. A formal communication and impact strategy will be developed with the support of the communication departments of participating institutions. Publications produced from IHCoR-Africa will be open-access in accordance with
NIHR policy. A publication policy will be agreed by all members of the IHCoR-Africa team prior to the first paper being published.

## Study status

Ethical approvals are in place for the study. Participant consenting and data collection is underway in both sites, beginning with blood pressure measurements. Screening of HMOD with reference standard and PoC tools will commence in December 2023. Data collection is anticipated to complete by mid-2024, followed by analysis and reporting.

## Data Availability

No data are associated with this article. When the results of this study are prepared and published, anonymised data will be made available in line with the policies of the NIHR, LSHTM, KWTRP and MRCG.
